### Trajectories of adolescents receiving the counselling component

Adolescents forming the cohort referred to counselling will complete assessments at the start of the counselling sessions and at two/three- and 12-month follow-up. Assessments include the Patient Health Questionnaire-9 for depression (38), the Generalised Anxiety Disorder scale-7 (GAD-7) (39), the SDQ follow-up questions to assess the impact of the intervention (40) and the Childrens Global Assessment Scale to assess functioning (41). We will select suitable measures for adolescents receiving counselling for nutritional/weight problems (e.g., food frequency questionnaire, physical activity questionnaire (42)). We will also explore counsellors and adolescents’ experience of the intervention with one-to-one semi-structured interviews.

## Ethics and dissemination

### Ethics

Written informed consent will be collected from adult participants (18 years and over) and from parents or guardians of adolescents under 18 years of age after explaining the study aims, procedure, risks, benefits, and rights. Assent will be obtained from all adolescents under 18 years of age.

The study is conducted in accordance with ethical principles that comply with the Declaration of Helsinki and the International Council on Harmonised Tripartite Guideline for Good Clinical Practice (GCP). Ethical approval for the project has been obtained from the University of Warwick. In addition, each site has obtained ethics approval from their Institutional Ethics Committees (IECs).

### Dissemination strategies

Our study findings will be shared through peer reviewed academic publications, national and international conference presentations, and practitioner and researcher networks. We will maximise the reach of our dissemination with bite sized research reports in layman format, public announcements in communities in LMICs, policy briefings, print and online media, and institutional and professional social media accounts and websites. We anticipate findings from the ISOBAR programme will influence local education and health systems through the implementation of a whole school intervention for mental and nutritional disorders which is accessible to all students regardless of gender, race and socioeconomic status. By implementing and evaluating the proposed intervention in two geographically and culturally distinct LMICs we will establish the contextual effect of the intervention providing evidence and recommendations to inform local, regional, and national policies.

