#### (2) Universal health literacy

The health literacy component is designed to improve knowledge, attitudes, and behaviours relating to mental well-being, nutrition, and physical health. It will be targeted at adolescents (e.g., classroom didactic and activity sessions, role playing, homework), parents (e.g., meetings) and school environments (e.g., improvements to school aesthetics, topics presented in assemblies). Each site has produced a bespoke health literacy training manual to guide counsellors in delivery. Manuals were developed in consultation with professionals in mental and nutritional health and draw on existing programmes from respective countries, e.g., the School Health and Wellness Programme in India (28), UNFPA’s Action for Adolescent Girls in Nigeria (29).

Manuals across sites share common content but also have variations (e.g., topics covered such as gender identity in India, and provision of breakfast and vegetable gardens in Nigeria, length and frequency of sessions) based on cultural adaptations and stakeholder engagement work. Common content across health literacy manuals includes: (1) understanding physical health (e.g., importance of physical activity, lifestyle diseases); (2) understanding the relationship between mental health and mental illness, and mental health and physical health; (3) nutrition for adolescents; (4) understanding stress, relationships, and common changes during growth; (5) common mental disorders in young people; and (6) coping mechanisms, treatment, recovery, and help-seeking.

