#### (3) Indicated counselling

All students identified as having serious or very high emotional or behavioural problems, with functional limitations as measured by the SDQ, and those children who did not screen positive on the SDQ but sought help, will be provided with in-school counselling within a month of the initial assessment. Sites are currently developing and piloting site-specific manuals to underpin the counselling component of the intervention. The manual will assist with the training of the counsellors and help ensure fidelity. Counsellors will be encouraged to develop a system of peer support across sites to facilitate mutual learning and enhance problem-solving skills. Counsellors will be trained to: (1) support young people with nutritional and/or mental health problems; (2) identify serious problems requiring specialist care and help young people to access that care; and (3) support teachers in schools to refer adolescents in need. Counsellors will use various techniques including problem-solving, active listening, and behaviour activation. Format and duration of counselling sessions will be tailored to adolescent need and severity of symptoms, with (one-to-one or group) sessions available for the duration of the project (or as needed) once the counselling is introduced into the intervention school). Adolescents will be referred for specialist care (e.g., psychiatric care) if there is no improvement during the counselling intervention period, or if the adolescent is demonstrating psychotic symptoms or suicidal ideation. Three counsellors per site will be recruited to deliver the intervention. Chennai and Gujarat will recruit graduates from mental health and social work fields as counsellors. Ibadan will recruit lay health workers due to a shortage of mental health professionals in the area.

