### Participants and recruitment

We will recruit adolescents from three schools per site (total = nine schools). The inclusion criteria are: (1) being a school going adolescent aged 12–18 years; and (2) willing to take part in the mental and physical health assessments. We will recruit approximately 200 adolescents per school, equalling 600 adolescents per site, and 1, 800 adolescents in total. In India, adolescents will be recruited from grades 6 to 8. Pilot work in Chennai and Gujarat indicates that this will equal approximately 200 adolescents per school. In Ibadan, adolescents will be recruited using stratified random sampling to reach the sample target number. Sites will continually monitor intervention roll out to allow improvements to be incorporated in real-time. Implementation strategies will include providing ongoing training and supervision for counsellors, local consensus discussions and educational meetings, creating a learning collaborative approach to capture and share local knowledge, and auditing the implementation processes to enhance participation and maintenance.

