### Analysis plan

We will conduct school-level and individual (cohort) level analysis. We will compare adolescents in the control and intervention schools to determine whether the health literacy intervention is associated with an increase in help-seeking. We will use non-randomised difference-in-difference (DID) analysis (34) to adjust for differences between schools (school-effects) and over time (time effects). The DID design is a quasi-experimental approach which enables the researcher to study causal relationships in settings where randomised control trials are unfeasible or unethical (35). Our outcomes are predominantly proportions (e.g., proportion seeking help), thus we will use a binomial-logistic regression model approach to estimate relative (odds ratios) and absolute (differences in proportions) effects of the intervention. The number of schools is likely too small to reliably estimate school-level random effects, so a mixed model is not considered. We will analyse our universal repeated assessments (administered to all adolescents in intervention and control schools) to determine the effects of the health literacy component on longitudinal mental and physical health measures (baseline, 8, 15, and 22 months). These data will be analysed using an individual level linear model with adolescent random effects, school, time and intervention fixed effects. We will conduct sub-analysis with the cohort of adolescents receiving counselling. The targeted cohort assessments (**Table 2**) will allow us to describe the trajectories of adolescents receiving the counselling component of the intervention to determine whether the counselling has an impact on mental and/or physical health outcomes. For the continuous cohort outcomes (“universal assessment”) the minimum detectable standardised effect size is approximately 0.1 assuming an individual autocorrelation coefficient between time periods of 0.8.

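### The claim that the study will establish a contextual effect is not identifiable, because country coincides with a different programme, workforce and sample

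*Protocol article*

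**What the plan says.** The closing claim, under Dissemination strategies, is that evaluation in two geographically and culturally distinct countries means "we will establish the contextual effect of the intervention providing evidence and recommendations to inform local, regional, and national policies". It carries no qualification.

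Other sections of the protocol article show what differs between the places to be compared:

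- **Content and dose** ((2) Universal health literacy). "Manuals across sites share common content but also have variations". The examples given are "topics covered such as gender identity in India, and provision of breakfast and vegetable gardens in Nigeria, length and frequency of sessions". Six content areas are common to all manuals.
- **Deliverers** ((3) Indicated counselling). "Chennai and Gujarat will recruit graduates from mental health and social work fields as counsellors", whereas "Ibadan will recruit lay health workers due to a shortage of mental health professionals in the area".
- **Delivery support** (text after Table 2). Project experts help the counsellors in Ibadan; no such help is mentioned for the Indian sites.
- **Recruitment** (Participants and recruitment). The Indian sites recruit from grades 6 to 8. "In Ibadan, adolescents will be recruited using stratified random sampling to reach the sample target number".

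In the Analysis plan, repeated universal measures go into an "individual level linear model with adolescent random effects, school, time and intervention fixed effects". Help-seeking is analysed by difference-in-differences with school and time effects. Neither description mentions a site or country contrast. The section on effectiveness of the health literacy component counts BMI and dietary behaviour among that component's effects.

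**The concern.** To say that context has an effect, one must compare the same programme in different settings, or at least be able to vary programme and setting separately. Here there are two countries, and the programme version, the workforce, the delivery support and the sampling method all change with country. If the intervention works better in one country, the data cannot say whether the setting, the add-ons, the type of counsellor or the sample made the difference.

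The claim has a stated use: recommendations at local, regional and national level. A policy maker told that context explains a difference would act differently from one told that the two countries ran partly different programmes. Diet and BMI show this most clearly. Breakfast and vegetable gardens sit inside the health literacy component in Nigeria, and the article describes no food provision in India. An overall diet or BMI estimate would therefore combine a programme with food provision and programmes not described as having it.

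**Working it through.** **1. The plan's own figure.** The only related figure is 80-90% power for help-seeking of 5% versus 11-12% with 200 adolescents per school. Significance level, sidedness, allocation and clustering are not stated. A pooled-variance comparison of two proportions without clustering, one-sided 5%, with 200 control and 400 intervention adolescents at one site, gives 80.9% (11%) and 89.4% (12%). Two-sided, the same sizes give 69.9% and 81.2%. So the figure can be reproduced under assumed inputs. The present point does not rest on it, but it shows that the sample was sized for a main effect, not for a difference between countries.

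**2. What lines up with country.**

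| Feature | Chennai | Gujarat | Ibadan |
|---|---|---|---|
| Named add-on content | gender identity | gender identity | breakfast, vegetable gardens |
| Session length and frequency | varies by site | varies by site | varies by site |
| Counsellors | graduates | graduates | lay workers |
| Expert help with delivery | not mentioned | not mentioned | yes |
| Recruitment | grades 6 to 8 | grades 6 to 8 | stratified random sample |

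The article attributes the gender identity topic to India as a whole. Write the effect in country *c* as core + context(*c*) + content(*c*) + workforce and support(*c*) + sample(*c*). The difference between countries is the sum of four differences, and two countries supply one contrast. That is one equation with four unknowns.

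**3. Rank check.** Inputs: nine schools, four time-points. The roll-out figure is not available, so one school per site is assumed to cross over at each follow-up. Fixed effects: 9 school + 3 time + 1 intervention = 13 columns.

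| Model | Columns | Rank |
|---|---|---|
| One intervention effect | 13 | 13 |
| + intervention by country | 14 | 14 |
| Three site-specific effects | 15 | 15 |
| Intervention by country + intervention by programme version (set at country level) | 15 | 14 |

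Site and country effects can be estimated. Context and programme version cannot be separated.

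**4. Precision of a country contrast.** Inputs from the article: 1,200 adolescents in India, 600 in Nigeria, 5% versus 11-12%. Assumptions: half the observations are exposed (under the assumed roll-out, 3 + 2 + 1 = 6 of 12 school-periods per site), one observation per adolescent, no clustering, two-sided 5%, all recruited adolescents in the denominator, and the same rates in both countries when computing variance.

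SE of a risk difference = √[(p₀(1−p₀) + p₁(1−p₁)) / (n/2)].

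- At 11%: Nigeria √(0.1454/300) = 0.0220; India √(0.1454/600) = 0.0156; contrast √(0.0220² + 0.0156²) = 0.0270. Detectable with 80% power: 2.80 × 0.0270 = 7.6 points.
- At 12%: 0.0226, 0.0160 and 0.0277; detectable difference 7.8 points.
- Interval for one site of 600: ±1.96 × 0.0220 to 0.0226, or ±4.3 to 4.4 points.

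If one country had the whole planned effect and the other none, that contrast of 6 or 7 points would be detected with power of about 60% or 72%. Clustering would lower this, as would a denominator restricted to adolescents above the referral threshold; use of repeated measurements could raise it. These figures show scale only.

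**The case against.** **It is a dissemination sentence.** The objectives and the two primary research questions contain no country contrast. The Conclusion claims only an initial assessment of effectiveness, and the Highlights and Phase 2 sections already limit causal inference. This bears on how prominent the problem is, but does not remove it. Those caveats concern the non-randomised roll-out; none says that country and programme coincide, and the sentence ties its claim to policy.

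**Context is studied elsewhere.** The evaluation guided by the Consolidated Framework for Implementation Research plans interviews, focus groups and a comparison across sites, and it counts counsellor background and the adaptation process as internal context. This stands: the work can describe and explore context, and under that broad definition workforce and adaptation belong to it. It still cannot isolate an effect of context on outcomes, and the sampling difference lies outside that definition.

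**Stronger readings that the article does not support.**

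- A reader might infer that a pooled intervention term causes the problem, or that no site contrast will be made. The Analysis plan lists one intervention term but does not exclude site terms, which may sit in an analysis plan that is not shown. Adding them would leave the confounding in place.
- A reader might infer that everything differs at every site. Chennai and Gujarat share counsellor type and grade-based recruitment, and all manuals share a common core.
- A reader might infer a special age range for Ibadan. The 12-18 inclusion range applies to all sites.
- A reader might infer that breakfast will drive diet or BMI results. The article gives no scale, duration or recipients, and food provision belongs to the component as defined. Crediting a diet effect to that component is therefore consistent with its definition; the difficulty is carrying it to sites not described as providing food.

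**Conclusion.** The point holds as a limit on what may be concluded. A country difference in effect cannot be attributed to context rather than to content, workforce, delivery support or sampling. This follows from the design as described, so no analysis plan can repair it. Local adaptation is legitimate; the fault is the inference promised from it.

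Its size is one unidentifiable parameter (rank 14 of 15), plus a detectable country difference of roughly 7.6 to 7.8 points against a planned main effect of 6 to 7. The rank result assumes the one-school-per-site roll-out, but the aliasing of country and programme version does not depend on the roll-out order. The precision figures rest on the simplifying assumptions listed in the working. The article gives no basis for estimating how large any bias in a pooled diet or BMI effect would be.

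**What to change.** 1. Replace the promise to establish a contextual effect with: to describe the effect of each locally adapted programme and to explore context.
2. State beside it that differences between sites combine setting, adaptation, workforce and sampling, and that the quantitative data cannot separate these.
3. Report site-specific intervention effects with intervals for help-seeking, diet and BMI beside the pooled estimate, as a description of heterogeneity. If the full analysis plan already contains these terms, a sentence saying so is enough.
4. Interpret Ibadan diet and BMI results as effects of a programme that includes food provision.
5. Assign the explanation of site differences to the qualitative evaluation, as exploratory.

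The cost is wording and a few extra model terms, with no new data. The drawback is that each site estimate rests on three schools, so the intervals will be wide, and the site terms will not remove the confounding.

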### Patient and public involvement

Stakeholder engagement is a core aspect of the ISOBAR project to ensure effective implementation. Early in the project, teams began developing a network of stakeholders including young people and their caregivers, school leaders and staff, counsellors, healthcare providers, commissioners, policy makers and community groups. During intervention development, the team have worked closely with adolescents, parents and teachers to culturally adapt (and amend following piloting) the intervention to site settings. Teams have worked with relevant educational organisations (e.g., Department of Education, Ministry of Education, Greater Chennai Corporation) and engaged with schools to consider infrastructure, willingness, resources, and timing of exam periods and holidays which could impact the delivery of the intervention.

The parents, teachers, and students provided information about their needs and the topics that they would like addressed in the sessions. The school administrators also discussed the feasibility of delivering the sessions in the school settings. Following the pilot phase, the students and teachers will provide feedback on the content and methodology for delivering the sessions. The teachers and school administrators will comment on the logistics of providing counselling services in the school setting. This process will be used to prioritise the topics to be discussed with adolescents within the broader ambit of adolescent mental and physical health. Stakeholders will be involved at key stages across multiple phases of the project, including intervention development, refinement, and implementation, providing input and feedback to guide adaptation and optimisation of the intervention. This iterative process will support alignment with local needs and enhance the relevance and potential scalability of the intervention.

## Conclusion

This hybrid implementation effectiveness study will contribute to the literature in the following ways: (1) provide detailed data on the cultural adaptation of school-based interventions in LMICs; (2) collate data on pragmatic implementation strategies as relevant to Nigeria and India; (3) provide initial assessment of the effectiveness of a combined school-based physical and mental health intervention for adolescents in LMICs; and (4) explore the potential cost effectiveness of this intervention. It is crucial that we understand the process of cultural adaptation and implementation of school-based interventions in local settings if we are to facilitate sustainability, replication, and scaling-up of these interventions in LMICs (20). Global mental health has only recently started focussing on the costs and benefits of interventions. We will collect real life costs rather than model these hypothetically, which will provide key information for adoption decisions at system and policy level (18).
